### Sample collection

Twelve-hour morning fasting (i.e., nothing to eat or drink except water 12 h prior) blood samples will be collected on the first day of each phase (baseline), and on days 41 and 42 of each treatment periods of the trial (in total nine times during the trial). This fasting blood samples (approximately 4 teaspoons or 20 ml) will be taken from the top of the forearm via venipuncture by a phlebotomist on each blood-draw day for assessment of blood biochemical markers. Each blood test will take approximately 5 min. No alcoholic beverages are to be consumed within 48 h prior to blood draws during the study periods. No food or caffeinated beverage consumption is allowed within 12 h prior to blood draws during the study periods. Blood samples will be centrifuged at 3000 rpm for 20 min at 4 °C, aliquoted to yield serum, plasma and RBCs, and then stored at − 80 °C until analyses.

Participants will be asked to collect 24-h urine samples at the first day of first phase and last day of each treatment period. Urine containers will be kept in the fridge during the day of collection, and then will be aliquoted and stored at − 80 °C until analyses. The volume of the 24-h urine samples and start and end time of collection will be recorded.

### Compliance

Compliance will be monitored, regarding participants having consumed the morning treatment smoothies on Tuesdays and Fridays, through visual affirmation by clinical coordinators. Participants will be required to return smoothie containers from other days’ smoothie treatments on the next visit. Also, participants need to fill out a treatment consumption checklist which include the date and timing of each treatment consumption and return the checklist at the end of each treatment period. Missed smoothie consumption or return of smoothie containers will be recorded for each participant. Non-compliance will be defined as missing supervision for, or failing to return the empty smoothie containers from, 80% of the total smoothies per treatment period. Missing two consecutive measurement or blood-sampling days will also be classified as non-compliance. Non-compliant participants will be asked to leave the trial. An intent-to-treat analysis will be performed to use the data from non-compliant participants.

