**Fig. 2 Fig2:**
[figure not shown]
Representation of the trial enrollment, interventions and analysis

During each treatment period, participants need to come to the RCFFN twice a week on Tuesdays and Fridays to consume one treatment under supervision and pick up treatments for the next 2 or 3 days. Each treatment consists of a frozen fruit smoothie (mango or pineapple), fruit juice (diet mango juice), sorbet and 25 g of protein from treatment-protein powder and the treatments will be consumed twice a day. HSP and the HSP+ powder has a green color and a stronger taste than casein-protein powder; however, our team has identified that by using a combination of frozen fruit and sorbet in the fruit smoothies this color and taste can be well-masked.

Participants will be instructed to consume two or less alcoholic beverages and no more than three 8-oz. cups of caffeine-containing beverages per day during the trial period. Participants will be instructed to perform their normal daily activities during the measurement day. Prolonged intense physical activity will be discouraged on measurement days and the days preceding measurement days. Participants will be strongly recommended to maintain consistency in their physical activities and dietary pattern during the trial period. A 3-day food record will be collected during the first day of the first phase and during the final week of each treatment period to be analyzed for calorie intake during the study.

During the study period, body weight will be monitored as a change could occur due to the inclusion of extra protein in a free-living condition. All outcome variables will be adjusted for changes in body weight should significant changes occur between treatments. Gastrointestinal tolerability and weekly monitoring questionnaires will be completed by participants weekly during each intervention period.

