### Study period

This study includes three phases of 6 weeks each, separated by two washout periods of 2 weeks. Participants will be involved in the study for a period of 22 weeks.

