### Statistical analysis

Statistical analysis will be performed in an intent-to-treat fashion. In addition, a per-protocol analysis will also be performed to check for potential effect attenuation due to unequal compliance or protocol deviations across treatments. Statistical analysis will be performed using SAS 9.4. The endpoint of treatments and baselines will be compared using a mixed-model analysis of variance. Sequence and sex will be included as fixed factors, and participant will be included as a random factor, with participant repeated by period.

Dunnett’s test will be used to adjust for multiple comparisons with the endpoint of the baselines set as the control. Effects of treatment by time on measures repeated during treatments will be assessed using a mixed-model analysis of variance with sequence, sex, time as fixed factors and participants included as random factors, with participants repeated by period, with Tukey-Kramer adjustments for multiple comparisons. Model residuals will be visually inspected to assess independence, normal distribution, and constant variance. Datasets with residuals determined to violate these assumptions will be transformed prior to re-analysis. Results will be expressed as estimated least square means ± standard error of the mean (SEM) for all values. Statistical significance will be set at *p* < 0.05 for all analyses.

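### The 80% in the non-compliance definition attaches to what is missed, so a participant with about a fifth of intake confirmed still counts as compliant

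*Protocol article*

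**What the plan says.** The Compliance section sets out two checks. Coordinators watch participants "having consumed the morning treatment smoothies on Tuesdays and Fridays, through visual affirmation by clinical coordinators". For the remainder, "Participants will be required to return smoothie containers from other days’ smoothie treatments on the next visit". A dated consumption checklist is also kept, and missed smoothies or containers are recorded for each participant.

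The criterion for non-compliance in a period is "missing supervision for, or failing to return the empty smoothie containers from, 80% of the total smoothies per treatment period". A separate ground covers absence from two measurement or blood-draw days in a row. Participants who are non-compliant are to leave the trial, and their data are used in an intent-to-treat analysis. The section on conditions for withdrawal also lists non-compliance as a ground for discontinuation.

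The schedule comes from two sections. Study design states that "the treatments will be consumed twice a day" and, on supervision, that "participants need to come to the RCFFN twice a week on Tuesdays and Fridays to consume one treatment under supervision". The length is given under Study period: "This study includes three phases of 6 weeks each".

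Under Statistical analysis, "a per-protocol analysis will also be performed to check for potential effect attenuation due to unequal compliance"; deviations from the protocol are named there as a second reason. The Discussion relies on strict compliance monitoring when it argues that any unblinding of participants is unlikely to affect the results.

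**The concern.** As the sentence is built, the 80% belongs to missed supervision and unreturned containers. A participant would have to miss four fifths of the product before being called non-compliant. No other place in the article gives a different threshold or says that 80% is the share to be consumed.

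The rule also uses one denominator, all smoothies in the period, for two checks that cover very different numbers of smoothies. Supervision applies to a small part of them, so a limit of 80% of the total does not fit it.

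Two uses are at stake. The rule triggers removal from the trial, and in a three-period crossover removal loses every later period; the plan recruits 35 to secure 30. It is also the only intake-based definition of compliance in the article, so it is the obvious basis for the per-protocol set.

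**Working it through.** The 80% is a definition, so there is no computed figure to reproduce. The check is whether it works on the protocol's own schedule.

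**Inputs**
- Smoothies per day: 2 (Study design).
- Period length: 6 weeks = 42 days (Study period).
- Supervised smoothies: 1 per visit, 2 visits per week (Study design, Compliance).
- Planned protein: 50 g/day (Objectives and hypothesis).

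**Counts per period**
- Total: 2 × 42 = 84.
- Supervised: 1 × 2 × 6 = 12, or 12/84 = 14.3%.
- Take-home: 84 − 12 = 72, or 72/84 = 85.7%.
- Threshold: 0.80 × 84 = 67.2, so first reached at 68 missed.

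**Misses of both kinds counted together (the most natural reading)**
- Non-compliant from 68 missed, that is, with 84 − 68 = 16 or fewer confirmed.
- Still compliant with 67 missed and 17 confirmed: 17/84 = 20.2%.
- Confirmed protein at that point: 17/84 × 50 = 10.1 g/day.
- Example: a participant who attends all 12 supervised visits and returns 5 containers (12 + 5 = 17) is compliant.

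**Containers alone**
- 68 of the 72 take-home containers must be unreturned: 68/72 = 94.4%.

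**Supervision alone**
- The most that can be missed is 12 of 84 = 14.3%, so this limb can never reach 80% of the total.

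**Sensitivity to the schedule**

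Taking 41 or 42 dosing days and 11 to 13 supervised visits, the supervised share runs from 13.1% to 15.9%, and a participant with 17 smoothies confirmed is compliant in every case.

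**For scale**

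If 80% was meant as the minimum to be taken, non-compliance would start at 17 of 84 missed (67 taken, below 67.2), that is 20.2%. As written it starts at 68 of 84, that is 81.0%.

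**The case against.** The best reply is that this is a drafting slip with limited reach. The primary analysis is by intent to treat and explicitly keeps data from non-compliant participants, so the threshold enters it only through later periods lost on removal; so lax a rule would remove hardly anyone. Actual intake can be analysed whatever the cut-off, because containers, checklists and supervised intake are all recorded. The rule on consecutive missed measurement days works as it stands. All of this is right, and it confines the point to the compliance definition and what depends on it.

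A second reply is that the Statistical analysis section neither defines the per-protocol set nor ties it to the 80% rule, and an analysis plan not shown here may do so. That also stands: the link is an inference. It does not remove the point, because the article states this threshold explicitly; it is a stated rule that does not work, not a detail left to another document.

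A reader might go further and take missed supervision to cover every smoothie drunk without supervision. Since 72 of 84 (85.7%) are unsupervised by design, everyone would then be non-compliant and the per-protocol set empty. The document does not support this. The Compliance section limits supervision to Tuesday and Friday mornings, so a take-home smoothie has no supervision to miss.

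Nor does the 20% figure describe a trial-level loss. If effect were proportional to intake (an assumption), one participant at 17 of 84 would show about 17/84 × 4 = 0.8 of the 4 mmHg target. One such person among 30 would lower the mean effect by about 3.2/30 = 0.11 mmHg. The article gives no reason to expect many.

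**Conclusion.** The point holds. As worded, the definition classes a participant as compliant with about 20% of intake confirmed (17 of 84 smoothies, about 10 of 50 g/day), and its supervision limb cannot be met. The threshold appears inverted. That an 80% minimum intake was meant is probable but not shown by the text. A rule this lax also undercuts the Discussion's appeal to strict monitoring.

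If the per-protocol set follows this definition, it would retain participants who took a fifth of the product and could not do the check for attenuation that is its stated purpose. The intent-to-treat analysis is largely unaffected.

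The counts rest on the stated schedule of two smoothies a day for 42 days with two supervised visits a week, and they change little with a day or a visit either way.

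**What to change.** For the per-protocol analysis, define a compliant period as a minimum share of the 84 scheduled smoothies confirmed by supervised intake or a returned empty container. If 80% taken was the intention, that is 68 or more of 84. If supervised attendance is to count as well, set its criterion against the 12 supervised visits, not against the total. Fix both before unblinding; the Blinding section keeps the code sealed until the primary-outcome analysis is finished, so this can be done without knowledge of treatment.

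For removal from the trial, the authors should reconcile the Compliance section with the conditions for withdrawal and state the rule they intend. No withdrawal threshold is proposed here.

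The cost is about one sentence for the per-protocol definition. The container returns, checklists and supervised-intake records that it needs are already collected.

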### Conditions for withdrawal from the trial

The following criteria are to be considered sufficient reason for discontinuing participation in the trial: non-compliance by the participant; developing condition(s) or consumption of supplements or medications as specified under the exclusion criteria or changing the type or dosage of the specified medications; presenting an adverse event or any other medical situation where, in the opinion of the qualified investigator, continuation of the trial treatment would compromise the participant’s health; abusive behavior of a participant towards trial staff; participant’s withdrawal of consent and self-removal from the trial for any reason. We will follow up with study participants who have been withdrawn from the trial due to an adverse event, until symptoms have resolved.

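### Non-compliant participants leave the trial, so later 24-h SBP readings are lost and the promised intent-to-treat comparison of treatments moves towards per-protocol

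*Protocol article*

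**What the plan says.** Three sections of the protocol article bear on this.

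- **Compliance.** Non-compliance is judged by period. One trigger concerns supervised intake and returned containers: missing supervision for, or "failing to return the empty smoothie containers from, 80% of the total smoothies per treatment period". The other concerns visits: "Missing two consecutive measurement or blood-sampling days will also be classified as non-compliance". The consequence and the promised analysis stand in consecutive sentences: "Non-compliant participants will be asked to leave the trial. An intent-to-treat analysis will be performed to use the data from non-compliant participants".
- **Conditions for withdrawal from the trial.** The list opens with non-compliance as "sufficient reason for discontinuing participation in the trial: non-compliance by the participant". What ends is participation in the trial, not only use of the product. The only follow-up stated after withdrawal is for adverse events, until symptoms resolve.
- **Statistical analysis.** "Statistical analysis will be performed in an intent-to-treat fashion". A per-protocol analysis is added to show whether unequal compliance or protocol deviations across treatments have attenuated the effect.

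Under Outcomes and measurement tools, the primary outcome, 24-h SBP, is read on the first day of the first phase and on day 41 of each of the three periods.

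**The concern.** An intent-to-treat analysis needs outcomes from participants who did not comply, in every period to which they were assigned. The removal rule ends collection of those outcomes. A later analysis plan cannot restore readings that were never taken, so this is more than a detail left open.

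A crossover makes the loss larger. Hypotheses 2 and 3 compare treatments, and that information comes mainly from differences within a participant across periods. Removal for poor compliance in one period also discards later periods on other treatments, in which the participant might have complied.

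The visit trigger widens the rule. Sample collection schedules blood draws on days 41 and 42, so missing that one pair of days is enough for removal, even with full smoothie intake and whole periods still to come.

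At stake are the meaning of the main analysis, the value of the comparison with per-protocol, and possible bias if removals are more frequent on one treatment.

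**Working it through.** **Inputs.** From Sample size: difference 4 mmHg, within-participant SD 5.45 mmHg, power 0.80, α = 0.05 (two-sided assumed), 30 required, 35 recruited. From Randomization: three periods and all six sequences. The documents give no non-compliance rate, so every count of non-compliers below is an assumption.

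**The plan's own figure.** With the SD of a within-participant difference equal to √2 × 5.45:

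n = 2 × [5.45 × (1.96 + 0.8416) / 4]² = 29.1, rounded up to 30.

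The stated 30 is reproduced. Recruiting 35 allows for a loss of 1 − 30/35 = 14.3%.

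**Contrasts kept by a non-complier.** The table gives the share of a given between-treatment contrast that survives, averaged over the six sequences.

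| Non-compliant in period | 1 | 2 | 3 |
|---|---|---|---|
| Outcome follow-up continues | 1 | 1 | 1 |
| Removed after that period's day-41 reading | 0 | 1/3 | 1 |
| Removed before that reading | 0 | 0 | 1/3 |
| Per-protocol set, taken as dropping that period and all later ones | 0 | 0 | 1/3 |

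The last two rows are the same. For a removed participant, intent-to-treat differs from this per-protocol set only by the day-41 reading of the non-compliant period, and not at all if removal comes first. A participant removed for missing days 41 and 42 has no day-41 reading for that period in any case.

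**Precision, assuming 5 of 35 are non-compliant.**

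- *All removed in period 1:* 30 complete pairs remain for each between-treatment contrast. The standard error rises by √(35/30) = 1.08, or 8%. Power falls from 0.857 to 0.798 (t-test, 2n − 4 degrees of freedom), or from 0.867 to 0.811 (normal approximation).
- *Spread evenly over periods, removed after day 41:* the average share kept is (0 + 1/3 + 1)/3 = 0.444, so there are 30 + 5 × 0.444 = 32.2 pairs and power is 0.838 (normal approximation).
- *Spread evenly over periods, removed before day 41:* the average share kept is (0 + 0 + 1/3)/3 = 0.111, so there are 30.6 pairs and power is 0.818.
- *Baseline contrasts:* with five period-1 removals after day 41, spread over treatments, each keeps about 30 + 5/3 = 31.7 pairs. The standard error rises by √(35/31.7) = 1.05, about 5%.

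**Direction of the estimate.** This is an illustration by simulation. It assumes a true hemp effect of −4 mmHg, no effect in a non-compliant hemp period, full compliance on casein, and a within-participant analysis.

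| Non-compliance per hemp period | 5% | 10% | 20% |
|---|---|---|---|
| Full follow-up | −3.80 | −3.58 | −3.15 |
| Removed after day 41 | −3.86 | −3.75 | −3.50 |
| Removed before day 41, same as per-protocol | −4.0 | −4.0 | −4.0 |

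Under these assumptions the first row should equal −4 × (1 − rate), that is −3.80, −3.60 and −3.20, so simulation error is about 0.05. The ordering is clear: removal shifts the nominal intent-to-treat result from its true value towards the per-protocol value.

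**The case against.** Several points on the other side have force.

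- **Baseline contrasts.** Hypothesis 1 compares each protein with baseline, and the Dunnett comparison uses baseline as control. A participant removed after a day-41 reading still contributes there. This stands, so the loss of contrasts described above applies to Hypotheses 2 and 3.
- **Power.** Placing all five removals in period 1 is a chosen worst case, and even then power is about the planned 0.80. Recruiting 35 was meant to absorb dropout. This stands: a reader might infer that the trial becomes underpowered, or that every standard error rises by 8%, and the documents support neither.
- **Intent-to-treat is not emptied.** A reader might infer that the two analyses become the same and the attenuation check is worthless. The documents do not support that. Earlier readings stay in the model. Compliance is assessed by period, so the day-41 value may already be in hand. Read literally, the smoothie threshold is missing 80% of a period's servings (0.8 × 84 ≈ 67), so partly compliant participants would remain. The article also does not define the per-protocol set.
- **Differential compliance.** Study design says the hemp powders taste stronger than casein, but the same sentence says the smoothie masks this well. Treatment-related removal is possible, not shown. The Discussion concedes that participants might tell casein from hemp, and the Statistical analysis section itself provides for unequal compliance.

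None of this answers the main point: the plan promises to use non-compliers' data and also stops collecting those data.

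**Conclusion.** The concern holds in a limited form. The removal rule and the intent-to-treat promise work against each other for the between-treatment comparisons. A participant removed in period 1 contributes nothing within-participant to Hypotheses 2 and 3, and one removed in period 2 contributes at most one of three contrasts. The main harm is to what the intent-to-treat estimate means and to the attenuation check, which is weakened but not void. Bias is possible if non-compliance differs by treatment. The cost in precision depends on an unstated non-compliance rate and, in the assumed example, stays within the dropout allowance. The two analyses coincide for the removed participants only if removal precedes day 41. The conclusion rests on reading the withdrawal section as ending outcome measurement, which is what its wording says and which no other text qualifies.

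**What to change.** Reconcile the Compliance, withdrawal and Statistical analysis sections by separating non-compliance from loss of outcome follow-up:

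- Record non-compliance, including missed measurement days, without making it a reason to end outcome measurement.
- Keep collecting the scheduled 24-h SBP and other outcomes in all remaining periods, unless consent is withdrawn or the qualified investigator decides otherwise for safety.
- Analyse every measured period by assigned treatment.
- Use compliance only to define the per-protocol set.

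Whether study product continues after non-compliance is for the investigators to decide and is not part of this request.

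The cost is a short amendment, which under Protocol modification needs principal investigator, REB and NNHPD approval. The visits are already scheduled. The change can help only participants not yet removed, and recruitment was due to finish in February 2020. The intent-to-treat estimate will also include more low-compliance data and so may be smaller, which is what that analysis is meant to show.

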### Study groups

Eligible participants will be assigned randomly to one of the following sequences: ABC, ACB, BAC, BCA, CAB or CBA. So, all the participants will be provided with all three treatments in a crossover design.

### Study period

This study includes three phases of 6 weeks each, separated by two washout periods of 2 weeks. Participants will be involved in the study for a period of 22 weeks.

### Outcomes and measurement tools

The primary outcome of this trial will be 24-h SBP, measured at the first day of the first phase and day 41 of each treatment phase using ambulatory BP monitors (ABPM, OnTrak, Spacelabs Healthcare Inc., Snoqualmie, WA, USA) [50, 51]. Participants will be fitted with an ABPM to wear for a full day. Continuous and SBP and DBP measured over 24 h will be recorded.

Office-measured BP, pulse-wave velocity and augmentation index will be determined using an automated oscillometric measurement device (Mobil-O-Graph, IEM, Stolberg, Germany) in an office setting at days 1 and 41 of each treatment phase [52, 53]. Office-measured BP will also be measured at day 22 to track the changes at the midpoint of each treatment phase. This measurement will take place in a quiet room while the participant is in a seated position with their arm resting on an arm rest at heart level. Participants will be advised to rest quietly throughout the measurements. Oscillometric measurement will be performed four times at 2-min intervals. The first measurement will be discarded, and the last three measurements will be averaged to determine office-measured BP. The LCD display of the oscillometric measurement device will be covered so that the participant is blinded to the BP values during the measurements. BP results will not be shared with participants until they have completed the trial.

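### On the Methods schedule, the end-of-treatment 24-h BP recordings run under alcohol, food and caffeine bans that the article does not state for the single baseline recording, so the contrast with baseline is not fully like with like.

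*Protocol article*

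**What the plan says.** All places are in the protocol article.

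- **Outcomes and measurement tools.** 24-h SBP is "measured at the first day of the first phase and day 41 of each treatment phase using ambulatory BP monitors". On duration: "Participants will be fitted with an ABPM to wear for a full day". There is one baseline recording in the whole trial and one endpoint recording per phase.
- **Sample collection.** Morning fasting blood is taken "on the first day of each phase (baseline), and on days 41 and 42 of each treatment periods of the trial", nine draws in all. Two rules surround each draw: "No alcoholic beverages are to be consumed within 48 h prior to blood draws during the study periods", and "No food or caffeinated beverage consumption is allowed within 12 h prior to blood draws during the study periods".
- **Study design.** At other times the everyday limits hold: "Participants will be instructed to consume two or less alcoholic beverages and no more than three 8-oz. cups of caffeine-containing beverages per day".
- **Inclusion criteria.** Fasting and abstention from alcohol, coffee and exercise are required before BP measurement. These rules make no distinction between baseline and endpoint.
- **Abstract, Methods/design.** The endpoint 24-h SBP is placed on the last day of each phase, which is day 42 of a 6-week phase, not day 41.
- **Objectives and hypothesis; Statistical analysis.** Hypothesis 1 is a fall in 24-h SBP from baseline under any of the three proteins, and Dunnett's test uses the baseline as control.

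**The concern.** A 24-h recording fitted on day 41 is still running on the evening before the day-42 draw. The participant is then barred from alcohol, and later from food and caffeine, while the monitor is recording. A recording fitted on day 1 has no draw the next morning. After the day-1 sample, the article leaves the participant free to have up to two alcoholic drinks, up to three caffeinated cups and an evening meal.

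The baseline recording is the sole comparator for Hypothesis 1. If the recording conditions move 24-h SBP at all, the movement enters all three protein-minus-baseline contrasts with the same sign. If it lowers SBP at the endpoint, it reproduces the pattern that Hypothesis 1 predicts. Randomising the treatment sequence does not balance it, because the baseline always comes first, and enrolling more participants does not shrink it. The section on anticipated results would read a fall under all three proteins as support for a simple message that adding protein lowers BP.

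**Working it through.** **1. The plan's own figure.** The Sample size section gives a 4 mmHg effect, within-participant SD 5.45 mmHg, power 0.80, α = 0.05 (taken as two-sided) and n = 30.

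n = 2 × 5.45² × (1.960 + 0.842)² / 4² = 29.1, rounded up to 30.

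The stated size is reproduced, so 5.45 is the SD of a single measurement within a participant and the variance of a difference is 2 × 5.45².

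**2. Overlap of the recording with the bans.** The article gives no clock times. Assume an 08:00 draw and monitor fitting between 08:00 and 14:00.

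- Day-41 recording, alcohol: the 48 h before the day-42 draw begin at 08:00 on day 40, so the ban covers the recording from fitting until the draw. That is 24 h if fitted at 08:00 and 18 h if fitted at 14:00.
- Day-41 recording, food and caffeine: the ban runs from 20:00 on day 41 to 08:00 on day 42, which is 12 h inside the recording for any of these fitting times.
- Day-1 recording, fitted at or after that morning's draw: 0 h under either ban, since no draw is scheduled on day 2.
- If the abstract's last day is followed and the monitor is fitted at or after the day-42 draw: 0 h under either ban, the same as baseline.

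**3. Weekday.** On exact day counts:

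- Day 41 is 40 days after day 1, and 40 mod 7 = 5.
- Day 42 is 41 days after day 1, and 41 mod 7 = 6. The weekday differs from baseline on either reading.
- Phases start 42 + 14 = 56 days apart, and 56 mod 7 = 0, so the three endpoints share a weekday with each other.
- Examples for day 41: a Monday start gives a Saturday endpoint, a Tuesday start a Sunday, a Friday start a Wednesday.

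**4. What a shift would do.** SE of one treatment-minus-baseline difference at n = 30: 5.45 × √(2/30) = 1.41 mmHg. For a shift b with no true protein effect, and Φ the standard normal distribution function, the probability of a significant two-sided result is Φ(−c + b/SE) + Φ(−c − b/SE). The values of b are assumptions.

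| Assumed shift b | b/SE | c = 1.96 (unadjusted) | c ≈ 2.35 (Dunnett, three contrasts) |
|---|---|---|---|
| 1 mmHg | 0.71 | 11% | 5% |
| 2 mmHg | 1.42 | 30% | 18% |
| 3 mmHg | 2.13 | 57% | 41% |

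With b = 0 the entries are 5% and about 2% per contrast. Because the contrasts share one baseline, the chance that at least one of the three is significant under Dunnett is higher: about 12%, 35% and 67%, against 5% with no shift.

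**The case against.** - **Two recording days are stated.** On the abstract's timing the restriction mismatch does not arise. This stands: the point is conditional on the Methods text, and the day-41/day-42 conflict is itself a defect. Methods is the more specific source, and the anthropometric and DXA measurements are also set on day 41, but the document does not settle it.
- **Clock times and visit windows are missing.** A reader might infer that alcohol is barred for the whole recording, that the fast fills exactly its last 12 h, or that baseline and endpoint can never share a weekday. The article does not support these as facts. The bans end at the draw, not at monitor removal, and the weekday result needs exact day counts. If day 1 were a Tuesday or Friday visit, day 41 would fall on a day with no supervised visit, so some flexibility in practice is plausible.
- **The article is condensed.** Instructions for the day-1 recording may stand in the full protocol. That is possible, so the claim is limited to what the article states. The abstention rules under Inclusion criteria do not close the gap: they precede measurement at both time points and do not govern the hours of recording.
- **The effect is probably modest.** What differs is at most two drinks, a capped caffeine intake and evening food, and much of the fast falls in sleep. A shift of 2 to 3 mmHg would exceed the 1.76 mmHg SBP reduction that the Background reports for replacing carbohydrate with protein. This stands against treating the upper rows of the table as likely.
- **Matching conditions does not rescue Hypothesis 1.** The baseline always comes first and there is no concurrent control, so confounding with time remains. This also stands.

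**Conclusion.** The point holds in a limited form. On the Methods schedule, the endpoint recordings lie largely under an alcohol ban and partly under a food and caffeine ban, and the article states neither for the hours of the baseline recording. On exact day counts the weekday differs as well. Under the abstract's timing only the weekday difference remains.

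It bears on the contrast with baseline alone. A reader might take it as a threat to the hemp-versus-casein or HSP+-versus-HSP comparisons. It is not, because the three endpoint recordings share the same restrictions and, on exact counts, the same weekday, so Hypotheses 2 and 3 are untouched.

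A reader might also infer that the design is shown to exaggerate the BP fall. The documents give neither the size nor the direction of an effect of these conditions. The per-contrast rates of about 5% to 41% under Dunnett (11% to 57% unadjusted) only illustrate assumed shifts of 1 to 3 mmHg against an SE of 1.41 mmHg. This is an avoidable systematic difference in one stated hypothesis that costs little to remove, not a flaw that invalidates the trial.

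**What to change.** 1. Reconcile the abstract and Outcomes and measurement tools on the day of the endpoint recording, and state when the monitor is fitted and removed relative to the blood draw.
2. If the recording overlaps the restriction windows, give participants the same alcohol, food and caffeine instructions, at the same clock times, during the baseline recording as operate during the endpoint recordings.
3. Where feasible, take the baseline recording on the same type of day (weekday or weekend) as the endpoint recordings will fall.
4. For baselines already recorded, state the difference in conditions whenever the contrast with baseline is reported. Recruitment was due to end about 29 February 2020, before the article appeared, so this may be the only step still open for many or all participants.

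The cost is a line in the participant instructions, one evening of restriction at baseline and slightly less freedom in scheduling that visit. No procedure is added and the sample size does not change. The lack of a concurrent control for Hypothesis 1 remains, so its result should be worded with that limit in view.
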